## STUDY FLOW CHART

[figure not shown]

## **1. INTRODUCTION**

### **1.1 Background: the problem**

Age, genetics and being overweight or obese are the three key contributory factors to the development of T2DM. Unlike age and genetic factors, people can affect their weight. Consensus now exists around weight loss in the region of 15kg (2-3stones) resulting in diabetes remission in a significant proportion of individuals with T2DM. Around 1% of the Scottish population is of South Asian ethnicity. South Asians are at higher risk of T2DM, developing the condition at a lower body weight than non-South Asians. This coupled with evidence that South Asians are less likely to access weight management services than non-South Asians points to a need for novel approaches to manage this growing problem. In the absence of appropriate management and support, the Scottish South Asian population would be at risk of developing health inequalities as well as the resulting health and health economic burden of sub optimal management of T2DM. A programme initially focusing on a low energy liquid formula diet is showing promising results both in terms of acceptability, weight change and impact on HbA1c. The formula food provides all essential nutrients in around 850kcal hence guarantees energy deficit and therefore weight loss with compliance. Many people appreciate the opportunity for a complete 'step away from food' and compliance is highly encouraging as compared with other weight management approaches due to the weight loss magnitude and associated clinical benefits such as reduction in fasting blood glucose and withdrawal of medications from as early as week one. The proposed study will examine if the initial phase of this approach using formula food products is acceptable to the South Asian population and if it results in similar clinical outcomes in terms of weight loss and diabetic status at the 3-6 month phase.

### **1.2 Rationale**

Currently one in every hundred people in Scotland are of South Asian ethnicity and weight management and T2DM are two significant health issues. However evidence suggests sub-optimal engagement and outcomes around weight management for the South Asian population. The cost of diabetic medications in Scotland is currently around £80 million per year and has doubled in the last 10 years, largely related to obesity. Figures therefore would suggest that just short of £1 million per year is spent on diabetic medications for the Scottish South Asian population of around 4500: NB this figure being conservative due to the higher risk of T2DM in the South Asian population. Without appropriate research and development in the South Asian population for this area of care, the cost of the burden of obesity will continue to multiply as well risking an increase in levels of health inequalities for this population. There is overwhelming evidence that modest sustained weight loss, e.g. current target of 5-10% prevents the onset of most new T2DM in people with prediabetes and it improves all aspects of diabetes control (glycaemia, blood pressure, lipids and microvascular damage with reductions in drug doses. Advice to lose and maintain 5-10% weight loss, by diet and exercise is included in most guidelines. However, most T2DM patients are now managed in primary care, many do not see a dietitian, and few achieve 5% weight loss.

### **1.3 Prior experience of managing obesity and type 2 diabetes**

Our recent work has shown that a greater level of weight loss of around 15kg achieves reversal of diabetes and normal blood glucose control from day to day in a significant proportion of people with diagnosed T2DM. Achieving this level of weight loss requires novel approaches such as use of formula products as part of a programme however the approach must be acceptable to the population being studied. The proposed study will assess if an existing evidence-based weight management programme, 'Counterweight-Plus', is acceptable to patients of South Asian origin and achieves weight change and T2DM as per non South Asian populations as compared with routine care. The primary focus is acceptability of TDR in this population and response in terms of weight change and remission of diabetes following the TDR. Initial findings will be used to inform a larger randomised controlled trial.

### **1.4 Study hypothesis**

Losing weight using a structured weight management programme which includes an initial period of total diet replacement, followed by carefully managed food reintroduction and then weight loss maintenance, is a viable treatment for putting T2DM into remission, and can potentially be transferred to a larger scale as part of routine GP care, where large numbers of overweight people with T2DM are managed in the UK.

## **2. STUDY OBJECTIVES**

The research will establish whether it is feasible and acceptable to offer patients of South Asian ethnicity an intensive weight management programme (known as Counterweight Plus) to achieve remission of diabetes. This study will provide data to support implementation of a larger randomised controlled trial aim at long term weight change in this population.

### **Research Questions**

- Can patients of South Asian ethnicity be recruited into an intensive weight management programme (known as Counterweight Plus)?
- Do patients of South Asian ethnicity engage, adhere to and continue in the initial 2 phases of Counterweight Plus, achieve weight loss, diabetes remission and improve quality of life?
- What do patients of South Asian ethnicity like/dislike or advise can be improved with the initial 3 phases (screening, total diet replacement and food reintroduction) of Counterweight Plus intervention?

## **3. STUDY DESIGN**

The study will follow a randomised controlled design with patients being randomised to either the weight management intervention or the control group. The control group will be asked to continue following usual management of type 2 diabetes for 3 months, prior to starting the intervention. This study will be performed according to

the Research Governance Framework for Health and Community Care (Second edition, 2006).

### **3.1 Study Population**

25 patients will be recruited and randomised to either control or intervention. Patients will be recruited from general practices in Glasgow that have a high population of patients of South Asian origin. GP patient lists will be screened to identify patients, aged 18-65 years diagnosed with type 2 diabetes within the previous 2 years (ideally newly diagnosed), who would be potentially eligible to participate. GP's will review these lists and remove any patients they feel would be ineligible or unsuitable to approach.

### **3.2 Inclusion criteria**

- Written informed consent
- Men and women aged 18-65 years
- South Asian ethnicities
- Body mass index (BMI)  $>25 \text{ kg/m}^2$  and  $<45 \text{ kg/m}^2$
- T2DM of duration 0-4 years (diagnosis based on a recorded diagnostic-level test: HbA1c and/or blood glucose)
- HbA1c  $\geq 48 \text{ mmol/mol}$  and/or fasting plasma glucose  $\geq 7 \text{ mmol/l}$  within last 12 months

### **3.3 Exclusion criteria**

- Current insulin use
- Recent routine HbA1c on record  $\geq 12\%$
- Weight loss of  $>5\text{kg}$  within the last 6 months
- Recent eGFR on record  $<30 \text{ mls/min/1.73}^2$
- Substance abuse
- Known cancer
- Myocardial infarction within previous 6 months
- Severe or unstable Heart Failure defined as equivalent to the New York Heart Association (NYHA):
  - Grade 3 - marked limitation of physical activity. Comfortable at rest, but less than ordinary activity causes fatigue, palpitation, or breathlessness, and
  - Grade 4 - unable to carry out any physical activity without discomfort. Symptoms of cardiac insufficiency at rest. If any physical activity is undertaken, discomfort is increased.
- or**
- Grade 2 if symptoms are not attributed to obesity - Slight limitation of physical activity. Comfortable at rest, but ordinary physical activity results in fatigue, palpitation, or breathlessness
- Learning difficulties
- Not fluent in English language
- Current treatment with anti-obesity drugs
- Diagnosed eating disorder or purging
- Pregnant/ considering pregnancy

- Patients who have required hospitalisation for depression or are on antipsychotic drugs
- People currently participating in another clinical research trial
- People with metal implants or devices and those who have claustrophobia cannot take part as MR scans are needed as part of the study

### **3.4 Identification of participants and consent**

Prior to recruitment of patients, GP practices will be approached by letter to invite their participation. In participating GP practices potential participants will be identified by a computerised search of GP records. An experienced research nurse, with a current research passport will undertake this. As Caldecott Guardians, GP's will be asked for permission/approval for the research nurse to search their database. All data will remain within the practice.

Searches will be undertaken at each GP practice and the list generated by the search screened by GP's before the letters are sent out on behalf of the practice.

Patients identified by GP's as potentially eligible to participate in the study will be sent an invitation to participate on behalf of their GP. The invitation will include a written information sheet providing details of study. Should they wish, patients will be able to contact their GP for further discussion. Patients will be asked to respond to the researchers to indicate whether or not they are interested in participating. Reply paid envelopes will be provided.

Patients indicating an interest in participating will be invited to attend for a screening appointment where the study will again be fully explained and discussed. Patients will be reassured that participation is voluntary and that withdrawal at any point would not affect their routine care. Patients fulfilling the inclusion criteria will then be asked to give their written consent to participate in the study and for clinical and outcome data to be extracted from GP records for up to 1 year from their initial appointment. These data will be extracted by the study research nurse. The consent form will be signed by both the patient and the research dietitian.

To maximise recruitment a reminder letter, plus the study information pack, will be sent to patients who have not responded at all to the initial invitation after 2 weeks.

We will also advertise the study via media platforms accessed by people of South Asian ethnicity (radio, press, social media). The advert will advise that recruitment for the study is ongoing, provide information on the eligibility criteria, and invite individuals interested in participating to contact the study team (phone number and e-mail provided) to discuss participation in more detail.

#### **3.4.1 Non respondents**

A screening log will be set up to record age, sex, BMI and duration of diabetes of all patients from the GP lists who are identified by the research nurse as satisfying the recruitment criteria for STANDby, and invited to participate. An anonymised list from

each GP practice detailing the age, sex, height and weight (to allow calculation of BMI), duration, or date of diagnosis, of diabetes and deprivation score (derived from postcode) of patients invited to participate, will be recorded. These data will be compared with the same data from patients who agree to participate in the study. This will allow reporting of the total number of patients invited to participate, the characteristics of those who decline, or do not respond to the invitation to participate, and determine differences, if any, between those who participate and those who do not. Such analyses are important to identify any recruitment bias and determine the representativeness of the study participants.

### **3.5 Withdrawal of subjects**

Patients who withdraw from the trial protocol will continue to have data collected from their routine diabetic clinic/GP visits, for up to 12 months from their initial appointment, unless they specifically withdraw consent for this. Data analysis will use best available follow-up weights (from routine attendances) and end of study diabetes status for subjects who discontinue the formal weight management programme. Drug intolerance, diet intolerance or poor-compliance will be recorded.

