| Primary Objective:   | To determine the feasibility and acceptability of an intensive weight management programme in South Asian patients to achieve remission of diabetes at 3 months.                                                                                                                                                                                                                                                                                                                                                                                                                                                                                                                                                                                                                                                                                                                                                                                                                                                                                                                                                                                                                                                                                                                                                                                                                                                                                                                                                                                                                                                                                                                                                                                                                                                   |

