| Primary Endpoint:    | Percentage achieving $\geq 15$ kg weight loss, and/or HbA1c $< 48$ mmol/l, off treatment, at end Total Diet Replacement stage to inform larger randomised controlled trial                                                                                                                                                                                                                                                                                                                                                                                                                                                                                                                                                                                                                                                                                                                                                                                                                                                                                                                                                                                                                                                                                                                                                                                                                                                                                                                                                                                                                                                                                                                                                                                                                                         |

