## **4 Trial procedures**

Patients will all be seen at the Glasgow Clinical Research Facility for all appointments.

Patients randomised to control will be advised to continue with usual care for 3 months before coming back to receive the intervention. They will be asked not to aim to lose any weight during the initial control period, but rather to wait until they commence the intervention part of the study. An appointment will be given to the patient for 3-months' time, and they will commence the intervention at that point.

Patients randomised to intervention will commence Counterweight Plus, which includes a TDR phase followed by structured food reintroduction. This will be delivered by research Dietitians experienced in programme delivery.

**TDR phase (0 to 12-20wks):** A commercial micronutrient-replete 825-853kcal/d LELD will be provided (Cambridge Weight Plan) to replace normal foods, with ample fluids, for 12-20 weeks. Oral hypoglycaemic agents (OHA), antihypertensive and diuretic drugs will be withdrawn on commencement of TDR, and reintroduced (according to guidelines) if diabetes or hypertension returns. Aspirin will be continued in patients prescribed this because of a previous MI (prior to the previous 6 months), but will be discontinued in patients who are prescribed it purely because they have T2D. Beta-blockers will be continued in patients prescribed these for the management of angina. A soluble fibre supplement (Fybogel 2x3.5g/day) will be prescribed to avoid constipation.

Participants will return for review one week after commencement on the TDR and at 2 weekly intervals thereafter till week 12-20 (total of 7-13 appointments) and the commencement of the food reintroduction stage.

To allow some flexibility for patients whose commitments, or practical limitations vary, the TDR phase will be permitted to continue up to 20 weeks if they fail to lose >15kg by week 12. Any patient whose BMI falls below 22 kg/m^2, before week 12 will be moved forward to 'food reintroduction and weight maintenance'. Reasons for moving to food reintroduction prior to week 12 will be recorded.

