#### **Appt 11 (Week 0+19, Final Appointment )**

- Venepuncture for HbA1c, urea and electrolytes, glucose, insulin, liver function tests, lipids.
- Measurement of weight & blood pressure
- Measurement of waist and hip circumference
- Psychological Process Questionnaire
- EQ-5D
- Process evaluation questionnaire
- MR, appetite hormone and Body Composition measurements if participant has consented to these

Final MR scanning will be undertaken at the point of maximal weight loss which will be either at the end of the TDR phase or end of food reintroduction

On completion of the study participants will be given advice, and written information, on maintaining weight loss, which will include goal setting, self-monitoring, physical activity, relapse prevention if weight tends to rise again, and education on food labelling and eating out. Participants will then be returned to the care of their GP, who will be informed.

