## **6.1 Sample size**

We aim to recruit 25 participants to the study. This figure has been chosen as this will give us enough information to assess the feasibility and acceptability of the programme to this population. We anticipate a failure to complete rate of about 25% (this may be greater at specific timepoints due to the COVID-19 pandemic). With 20 participants in a randomized comparison, the study can estimate the change in weight with a margin of error of 2.8kg assuming a standard deviation weight change over 3 months of 6kg. e.g., for an average observed weight change of 8kg (SD 6) we can estimate with 95% confidence that in the population the true weight change would lie between 5.1 and 10.7kg.

The proportion achieving remission in the combined intervention and delayed intervention groups (n=20) will be compared to the proportion achieving diabetes remission in the external DIADEM-1 trial control group (Taheri et al, Lancet Diabetes and Endocrinol, 2020) (12%; 95%CI 5%, 21%). Therefore assuming 12% remission in a usual care group (based on DIADEM), using a one sample proportion test, with 20 participants there will be 83% power to detect a significant difference if 30% of participants (n=6) or more achieve remission.

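### Section 3.5 reads participants who discontinue at end of study and on an unwindowed routine weight, while the primary endpoint is read at the end of TDR, so the primary result can mix time points

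*Protocol*

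**What the plan says.** Section 3.5 gives the only rule in the protocol for analysing people who stop the programme: "Data analysis will use best available follow-up weights (from routine attendances) and end of study diabetes status for subjects who discontinue" it. Routine data on those who withdraw are collected "for up to 12 months from their initial appointment, unless they specifically withdraw consent for this".

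The primary endpoint in the Study Synopsis is the percentage meeting a weight-loss threshold of 15 kg and/or an HbA1c threshold of 48, "off treatment, at end Total Diet Replacement stage". The primary objective speaks of an "intensive weight management programme in South Asian patients to achieve remission of diabetes at 3 months".

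End of TDR is nominally week 12, but section 4 lets it move: "the TDR phase will be permitted to continue up to 20 weeks if they fail to lose >15kg by week 12". The end of study is a later visit, listed in section 4.1 as "Appt 11 (Week 0+19, Final Appointment". Bloods including HbA1c are scheduled at both visits (section 4.1 and Appendix A), and section 4.3 asks GPs to repeat HbA1c at both.

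On attrition, section 6.1 says: "We anticipate a failure to complete rate of about 25" per cent, and adds that the pandemic may raise it at particular time points.

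**The concern.** This is a stated rule, not a detail left to the SAP. The protocol defines an end-of-TDR assessment and requests the data for it, yet directs that diabetes status for people who discontinue be taken from a different, later assessment. It makes no exception for the primary endpoint.

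Three things follow.

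- For diabetes status the mismatch is explicit. Status at the end of TDR and status after food reintroduction are different quantities, and the later one would be used only for those who stopped.
- For weight the mismatch is possible rather than certain. A best-available routine weight has no window and no order of preference, so it may fall close to the end of TDR or months away from it. Because 15 kg is a threshold, the choice among several weights can change whether a person counts as a responder.
- A participant who finishes TDR and stops during food reintroduction has discontinued the programme. Taken literally, section 3.5 replaces that person's valid end-of-TDR status with a later one.

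The responder percentage is meant to inform a larger trial, so what it measures should be clear.

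**Working it through.** The protocol gives no figure for this point, so there is none to reproduce. The check sets the time points side by side and then sizes the number of people involved.

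**Time points**

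| Item | Time | Source |
|---|---|---|
| Primary endpoint | End of TDR: week 12, up to week 20 | Study Synopsis; section 4 |
| Primary objective | 3 months | Study Synopsis |
| Diabetes status if discontinued | End of study: nominally week 19 | Sections 3.5 and 4.1 |
| Weight if discontinued | Any routine attendance, no window | Section 3.5 |
| Limit on routine data | 12 months from initial appointment | Section 3.5 |

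Nominal gap for diabetes status: 19 − 12 = 7 weeks.

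**Number affected**

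- Sample size 25 and failure to complete about 25% (section 6.1): 0.25 × 25 = 6.25, so about 6 people.
- Weight of one person in the responder percentage: 1/25 = 4 percentage points. On the 20 participants that section 6.1 uses for remission, 1/20 = 5 points.

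**Leverage of one person (scale only)**

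Section 6.1 compares remission in 20 participants with 12%. The exact one-sided binomial tail probability against 12% is 0.083 for 5 of 20 and 0.026 for 6 of 20. One classification can therefore move such a comparison across a conventional threshold. This shows how much one person counts. It does not estimate the effect of the timing rule, and section 6.1 names no visit for that comparison.

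**Mean weight change (scale only)**

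The stated margin of error reproduces: t(0.975, 19) × 6/√20 = 2.093 × 1.342 = 2.81 kg, against 2.8 kg in section 6.1. If a quarter of participants are read at a later time, each 1 kg difference between their end-of-TDR and later weights moves the overall mean by 0.25 × 1 = 0.25 kg. The documents give no regain figure. On an assumed difference of 2 to 6 kg, the shift is 0.25 × 2 = 0.5 kg to 0.25 × 6 = 1.5 kg.

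**The case against.** The best counter-argument is that section 3.5 speaks of data analysis in general and does not name the primary endpoint. Every participant has an end-of-study assessment, and the remission definition in section 4.2 names no visit. The sentence could therefore be meant only to fill in the end-of-study assessment, in which case nothing is mixed. Windows and missing visits are also commonly left to the SAP, which section 6.2 promises and which is not at hand. This reading is possible, but the protocol does not state it: the sentence has no exception, and no other rule covers these people. An SAP that follows the sentence inherits the mismatch; one that departs from it contradicts the protocol.

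Other objections stand and limit the point:

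- A reader might infer a gap of about 40 weeks (52 − 12). The documents do not support that as the usual case. Twelve months is the period over which routine data may be collected; the final appointment is nominally week 19.
- A reader might infer that a control who leaves is read 9 months after the 3-month comparison (12 − 3). The sentence concerns people who discontinue the weight management programme, and a control who leaves in the first 3 months has not started it. It does not clearly apply to them.
- A reader might assume 5 remissions among 19 completers and quote 5/25 = 20% to 11/25 = 44%. That is a missing-data envelope, from none to all of six leavers in remission, on an invented starting count. It does not measure the effect of changing the time point.
- The phrase about best-available weights need not mean picking a favourable value. It more naturally means using whatever routine care provides, and following people after they stop is sound practice. The weakness is only that no selection rule is fixed.
- Those who complete are not on one date either, since the end of TDR moves between weeks 12 and 20.

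**Conclusion.** The point holds in a limited form. As written, section 3.5 assigns people who discontinue a later diabetes status than the primary endpoint calls for, and a weight with no fixed time. The primary result can therefore mix time points for up to about a quarter of participants: at most about 6 of 25 at the anticipated attrition rate, each worth 4 percentage points. The nominal gap is 7 weeks, and it lengthens only if later routine data within the collection period are used.

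This rests on reading section 3.5 as governing the primary endpoint, which is its plain sense but is not spelled out, and on the 25% rate, which the protocol says may be exceeded at some time points. The number actually affected falls if routine values happen to lie near the end of TDR. The direction of bias is unknown: later values may include regain, or further loss under routine care.

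The study is a feasibility study and is not powered for a primary outcome, so this does not undermine the design. It should be corrected because the result feeds the planning of a larger trial and the correction is cheap.

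**What to change.** Amend the sentence in section 3.5, and carry it into the SAP, so that for the primary endpoint:

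1. Any end-of-TDR weight and HbA1c already obtained is kept, even if the participant stops later.
2. Otherwise, the routine weight and HbA1c nearest a fixed nominal time are used: week 12 after starting TDR, which matches the 3-month objective. They must fall within a window set before the data are seen. A fixed week is needed because the end-of-TDR date is undefined for someone who leaves early.
3. A participant with no value in the window stays in the denominator as not meeting the endpoint, with an observed-case sensitivity analysis alongside. Counting such people as non-responders is one convention among several; what matters is that it is stated.
4. End-of-study status and later routine values are reported as separate outcomes.

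The documents give no basis for a particular window width; the team should choose one with the expected frequency of routine attendances in mind.

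The cost is one sentence, and section 4.3 already asks GPs for HbA1c at both time points. The responder percentage may be slightly lower, and some late routine values leave the primary analysis. The change does not put those who complete on a common date, because their end of TDR still varies from week 12 to week 20.
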